**Methods:**

This is a protocol of a 4-week prospective randomised controlled parallel pilot trial in people post stroke at the chronic stage with limited upper ankle joint mobility and an impairment in balance and mobility. At a German outpatient therapy centre using 1:1:1 allocation, 36 patients will be randomised into one of three groups: 15-min talocrural joint MT plus 30-min specific TOT (group A), 45-min specific TOT (group B), and controls (group C). Training will be goal-oriented including tasks that are based on daily activities and increased in difficulty utilising predefined progression criteria based on patients’ skill levels. Interventions will be provided face-to-face 2 times per week, for 4 weeks, in addition to 20-min concurrent x4 weekly home-based training sessions. Data will be collected by blinded assessors at baseline, post-intervention and 4-week follow-up. The primary outcome will be feasibility assessed by recruitment, retention and adherence rates, compliance, adverse events, falls and the acceptability of the intervention. Secondary outcomes will be walking speed, single and dual tasking functional mobility, ankle range of motion, disability and health-related quality of life.

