### Data collection

Demographic (gender, age) and stroke-specific data (lesion side; disease duration; modified Rankin scale score) will be extracted from patients’ charts at eligibility screening (−*t*_1_). Study-specific assessment data will be collected at baseline (*t*_1_), post-intervention (*t*_2_) and follow-up (*t*_3_) at 4 weeks after completion (Table 3) by two physiotherapists blinded to the study intervention. Assessments will be performed at similar times to increase comparability. In addition to ROM measurement, the validated German version of all assessments will be used. Semi-structured interviews will gather in-depth information regarding acceptance of the study intervention. Changes from baseline and from post-intervention will be evaluated for all outcomes using means, medians, proportions and text as appropriate.

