#### Sample size

The study will be a pilot RCT to provide information for a subsequent larger RCT. The sample size was based on specific objectives of the study such as feasibility, acceptability and falls rather than on estimated effects of interventions. Julious recommends a minimum sample size of 12 patients per group for pilot studies [52]. Therefore, 36 people post stroke will be recruited into three groups (A, B and C). Taking into account an attrition rate of 20% and using the equation $$ N=\frac{n}{\left(1-\frac{z}{100}\right)} $$ where *n* is the sample size of 36 patients and *z* is the expected attrition rate [53], this number may increase to a total of 45 patients. For the sample size estimation of the main trial, imprecision of the standard deviation in small samples will be taken into account [54].

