### Data analyses

#### Statistical analysis

IBM SPSS Software, release 26.0 (IBM Corporation, Armonk, NY, USA) and GraphPad Prism 8, San Diego, CA, will be used for the data analyses. Statistical significance will be defined as a two-tailed *p*-value <0.05. The percentage of missing data will be recorded. Using Little’s test of missing completely at random (MCAR) [55], the data will be checked, signified by a *p*-value >0.05. An intention-to-treat analysis will be performed.

Descriptive statistics will be used for the baseline demographic variables, primary and secondary outcomes. Continuous data will be checked for normal distribution using the Shapiro-Wilk Test, Q-Q plots and histograms. Raw count (number (*N*), %) will be presented for counted (*N* females and males, *N* falls and *N* adverse events if any), compliance (types and order of home exercises, *N* of repetitions and deviations from the protocol) and nominal data (gender, recruitment, retention and adherence rates). Medians (range; 25th and 75th percentiles) will be reported for ordinal data (Mini BESTest if there are missing data, SIS); mean (95% confidence interval (CI)) will be reported for continuous data (age, Mini BESTest if data can be transformed into interval level, 10MWT, TUG, TUG_manual_, TUG_cognitive_, ankle ROM measures).

The recruitment rate (%) will be estimated by dividing the number of consenting patients by the *N* of eligible patients, multiplied by 100. The retention rate determined by dividing the *N* of patients who completed the study by the *N* of the total sample, times 100. Adherence rates will be calculated by dividing the *N* of TOT sessions (8x; 16x) performed by the patients, divided by the *N* of the scheduled (face-to-face; home-based) training sessions over the 4-week study period, times 100 [56]. The eligibility, recruitment and adherence rates will be calculated with their 95% CI according to the Wilson “score” method cited by Newcombe [57]; when the proportion is close to 0 or 1, a Poisson approximation as described by Brown and colleagues will be used [58].

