Inductive statistics will detect any trends related to the intervention efficacy acting as a basis for the sample size calculation for a larger main study. The sample size estimation will be based on a power of 80%, an alpha of 5% and the standardised effect size (Cohen’s *d*). Cohen’s *d* will be calculated using the formula *d* = (mean 1−mean 2)/corrected pooled SD. The corrected pooled SD for 80% of trials will be determined using the formula $$ {SD}_{corrpool}\sqrt{\left(\frac{SD{1}^2+ SD{2}^2}{2}\right)}\ast 1.293 $$ [54]. Effect sizes will be estimated with 95% CI using an effect size calculator provided by the Centre for Evaluation and Monitoring at the University of Durham, UK [59].

Baseline group differences will be examined using the chi-square test for nominal data, Kruskal-Wallis test for ordinal data and one-way analysis of variance (ANOVA) for continuous data. If a non-normal data distribution is observed in continuous data, data transformation or non-parametrical tests will be performed, as appropriate. Kruskal-Wallis test will evaluate differences between groups and time points, followed by a Bonferroni correction for multiple comparisons. On continuous data, test assumptions for a mixed design ANOVA will be reviewed, with standard correction procedures employed appropriately. In order to evaluate the effects of the intervention on walking speed, mobility, dual-task mobility and ankle ROM, a 2-way mixed design ANOVA will be used, with “time” (*t*_1_, *t*_2_ and *t*_3_) as within-subject factor and “group” (A, B and C) as between-subject factor. If the overall group-by-time interaction is statistically significant, post hoc tests with Bonferroni correction will be applied to determine group differences in pairwise comparisons.

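### Kruskal-Wallis is planned for differences between time points, but the visits are repeated measures on the same patients: the wrong test for the time comparison on the ordinal outcomes

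*Protocol article*

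**What the plan says.** In the protocol article, the Statistical analysis section sets out the non-parametric comparison in one sentence: "Kruskal-Wallis test will evaluate differences between groups and time points, followed by a Bonferroni correction for multiple comparisons". The significance rule is: "Statistical significance will be defined as a two-tailed *p*-value <0.05".

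The Data collection section fixes the visits. The study assessments "will be collected at baseline (*t*_1_), post-intervention (*t*_2_) and follow-up (*t*_3_) at 4 weeks after completion", so each patient contributes three measurements. The same section adds: "Changes from baseline and from post-intervention will be evaluated for all outcomes using means, medians, proportions and text as appropriate".

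The Statistical analysis section treats the SIS as ordinal. It treats the Mini BESTest as ordinal when data are missing and as continuous when scores can be converted to interval level. For non-normal continuous data it allows either transformation or a non-parametric test, as appropriate. Walking speed, mobility, dual-task mobility and ankle range of motion go to a mixed ANOVA in which time is the within-subject factor and group the between-subject factor. Neither the SIS nor the Mini BESTest is in that list. No paired rank test is named anywhere in the article.

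**The concern.** Kruskal-Wallis ranks all observations together and judges the rank sums as if every observation came from a different person. Groups A, B and C at one visit meet that condition. The three visits do not, because every patient appears in each. Differences between patients then stay in the error term, although a comparison over time should remove them.

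The paragraph therefore handles one design in two incompatible ways: time is paired for the continuous outcomes and unpaired for the ordinal ones. At stake is a reading of no change over time in disability and quality of life (SIS), and possibly in the key secondary outcome, that comes from the test rather than the data.

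**Working it through.** **The plan's own figure.** The only computed sample-size figure is the attrition-adjusted total: N = n/(1 − z/100) = 36/(1 − 0.20) = 45. It reproduces and does not depend on this test. The article gives no power or error rate for Kruskal-Wallis, so there is none to reproduce.

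**Inputs from the article.** Three visits on the same patients (Data collection); two-sided 5% level (Statistical analysis); 36 patients in three groups, 12 per group (Sample size).

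**Assumptions, not in the article.** A common between-visit correlation ρ, and a shift d in SD units, the same at t2 and t3. Scores are multivariate normal. Ranges are shown because the article gives neither ρ nor d.

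**Why the level is missed.** The difference between two visit means on the same n patients has variance 2σ²(1 − ρ)/n. An independent-samples test works with 2σ²/n. The true variance is thus (1 − ρ) times the assumed one: half at ρ = 0.5 and one fifth at ρ = 0.8. The statistic is too small and the test rejects too rarely.

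**Simulation.** 20,000 runs per setting. Kruskal-Wallis across the three visits is compared with Friedman, which takes patients as blocks. Both are referred to chi-square with 2 df at 0.05.

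| n | ρ | d | Kruskal-Wallis | Friedman |
|---|---|---|---|---|
| 12 | 0 | 0 | 4.8% | 6.1% |
| 12 | 0.5 | 0 | 0.6% | 5.7% |
| 12 | 0.7 | 0 | 0.1% | 5.9% |
| 12 | 0.8 | 0 | near 0 | 6.4% |
| 12 | 0.5 | 0.5 | 10% | 31% |
| 12 | 0.7 | 0.5 | 7% | 47% |
| 12 | 0.8 | 0.5 | 5% | 65% |
| 12 | 0.8 | 0.8 | 36% | 96% |
| 12 | 0.8 | 1.0 | 67% | over 99% |
| 36 | 0.8 | 0.5 | 49% | 99% |
| 36 | 0.8 | 0.8 | over 99% | 100% |

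The rows with d = 0 are type I error and the rest are power. With ρ = 0 the Kruskal-Wallis level is correct, so the dependence between visits is the cause. Rounding scores to a 0–28 scale (assumed mean 16, SD 5) gave nearly the same Kruskal-Wallis and power results, and put Friedman's level at 4.6% to 4.8% for n = 12.

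**Use between groups.** With 12 per group at one visit and no effect, Kruskal-Wallis rejected in 4.8% of runs. That use is sound.

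**A third reading.** If all nine group-by-visit cells were ranked in one test, the level with no effect would be 4.4% at ρ = 0.5 and 7.1% at ρ = 0.9. The conservative direction therefore belongs to the comparison of the three visits.

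**The case against.** The wording may mean group comparisons at each visit, or of change between visits. Both are valid, and the authors clearly know that visits are paired, since they say so for the mixed ANOVA. This is possible, but the sentence does not say it. On that reading the ordinal outcomes would have no named test of change over time, so the sentence needs correcting either way.

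The objection on scope stands. A reader might infer that every non-normal continuous outcome goes to this test. The article offers transformation or an unnamed non-parametric test, so only the SIS is certain. The Mini BESTest depends on missing data, and the continuous outcomes sent to the mixed ANOVA have time handled correctly.

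The objection on consequences also stands. Feasibility is the primary outcome. The main-trial sample size is to come from Cohen's d with a corrected pooled SD, not from this p-value. Medians and quartiles will be reported for ordinal data, so change stays visible descriptively, and the article calls all its results preliminary. The sentence on changes in Data collection concerns summaries only and is not itself at fault.

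**Conclusion.** The test is wrong as written for the comparison of time points, and right for groups at one visit or on change scores. This is a named test assigned to a comparison that it does not fit, not a detail left to a fuller document.

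The loss is large for modest change in a small arm and also substantial with patients pooled. For a 0.5 SD shift, power is 10% to 5% against 31% to 65% in one arm of 12 (correlation 0.5 to 0.8), and 49% against 99% with all 36 at correlation 0.8. Correlation and shift are assumptions.

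A reader might infer that the plan could hardly detect any change. The figures do not support that: power is about 67% for a 1 SD shift with 12 patients and over 99% for 0.8 SD with 36, both at correlation 0.8. Nor does the visit comparison produce excess false positives; it misses real change.

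Feasibility, the 36 and 45 patients and the effect-size calculation are unaffected. This is a should-fix correction to exploratory secondary analyses.

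**What to change.** Delete the reference to time points from the Kruskal-Wallis sentence. For ordinal outcomes, and for continuous ones analysed by ranks, state two analyses:

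- Change over time within patients: Friedman test across t1, t2 and t3, followed by Wilcoxon signed-rank tests with Bonferroni correction.
- Differences between groups: Kruskal-Wallis on change from baseline, t2 − t1 and t3 − t1.

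The cost is a one-sentence rewrite. It needs no new data, visits or patients.

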#### Randomisation, concealment of allocation and blinding

Randomisation will be stratified on age, the most relevant predictive factor for balance and mobility change in people post stroke (strata: under 70; 70 and over) [24]. Stratification will help ensure similarity between the intervention and control groups regarding age. Mixed randomisation will be performed on the two age groups, consisting of simple and blocked randomisation [25] and applying the following procedure: (1) permuted blocks of three or six are generated with an online random number generator (Sealed Envelope, London, UK); (2) after having randomised a predefined, small and varying number of patients to the three groups, a block size of an interspersed uneven block of 5–11 is chosen, with predefined differences in the sample sizes of the allocated groups; (3) a simple randomisation sequence is generated using the same random number generator; and (4) uneven distribution of As, Bs and Cs provided, another set of permuted blocks of three or six is generated. Details of blocking will be kept in a separate, unavailable document.

Allocation concealment will be performed to avoid allocation bias. Each patient will receive a unique identification number (ID). Based on the randomisation list, sequentially numbered sealed opaque envelopes including group allocation numbers A, B and C will be created for each stratum, given to patients in the order they are recruited. Patients will be asked not to discuss their allocation until study completion. Should a patient nonetheless report details of his or her group allocation, the patient will be informed about the importance of blinding and asked again not to tell anybody about the allocation. In such a case, a second assessor will perform the assessments. The allocation sequence and sealed envelopes will be created by a researcher who is not involved in the study procedures (BS). Patients will be assessed for eligibility and enrolled by the chief investigator (FS) and assigned to the intervention or control groups by the care provider, a physiotherapist-researcher (KT). Outcome assessors (EB; EK) will be blinded to the group allocation of patients. It will not be feasible to blind the care provider.

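### The planned mixed-design ANOVA is valid with complete data but less precise than it could be: baseline is an outcome level, the stratification factor age is left out, and pairwise tests wait on a 4-df interaction

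*Protocol article*

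**What the plan says.** The Statistical analysis section of the protocol article fixes the model: "to evaluate the effects of the intervention on walking speed, mobility, dual-task mobility and ankle ROM, a 2-way mixed design ANOVA will be used". The three visits, baseline included, are the levels of the within-subject factor, and group (A, B, C) is the between-subject factor. No covariate is named. On pairwise comparisons it says: "If the overall group-by-time interaction is statistically significant, post hoc tests with Bonferroni correction will be applied".

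The section on randomisation says: "Randomisation will be stratified on age, the most relevant predictive factor for balance and mobility change in people post stroke". The strata are under 70 and 70 or over.

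On the analysis population, the Statistical analysis section says only: "An intention-to-treat analysis will be performed". It adds that the percentage of missing data will be recorded and that Little's MCAR test will be run. It names neither imputation nor a complete-case rule. The Sample size section plans 36 patients, 12 per group, and allows for 20% attrition by recruiting up to 45.

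**The concern.** Four features of the named model each cost something.

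- **Baseline.** The first visit is a level of the time factor, so a group effect is estimated through change from baseline. Adjusting for baseline as a covariate is more precise whenever the correlation between visits is below 1.
- **Age.** The trial stratifies on age because it is held to predict change, and then leaves age out of the analysis of change.
- **Missed visits.** A classical repeated-measures ANOVA needs all three visits from each patient. Unless values are imputed, a patient seen post-intervention but not at follow-up is lost altogether.
- **Interaction gate.** Task-oriented training with or without manual therapy (A versus B) is the comparison in the trial's title. Its post hoc test is reached only through an omnibus test spread over three groups and three visits.

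At stake is the width of the intervals around preliminary effects in a small trial. No feasibility criterion depends on this model.

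**Working it through.** **Inputs from the protocol article.** 12 patients per group, 36 in total; attrition 20%; three visits; three groups; two-sided alpha 0.05.

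**Assumptions, not in the article.** Common SD at all visits; equal correlation r between visits, 0.5 to 0.8; for the power figures, the effect sizes and age effects stated below, with half the patients in each age stratum.

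**1. The plan's own figure.** 36 / (1 − 20/100) = 45, which reproduces. At 20% attrition, 45 × 0.8 = 36 patients remain with complete data, 12 per group.

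**2. Degrees of freedom of the gate.** (3 − 1) × (3 − 1) = 4.

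**3. Baseline as a level or as a covariate, one post-baseline visit, complete data.** With n per group, the variance of a group difference is:
- change from baseline: (2/n) × 2σ²(1 − r)
- baseline-adjusted: (2/n) × σ²(1 − r²)

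The ratio, adjusted to change, is (1 + r)/2.

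| r | (1 + r)/2 | variance saved | change-to-adjusted ratio, simulated at 12 per group |
|---|---|---|---|
| 0.5 | 0.75 | 25% | about 1.3 |
| 0.7 | 0.85 | 15% | about 1.13 |
| 0.8 | 0.90 | 10% | about 1.07 |

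The inverses of the formula are 1.33, 1.18 and 1.11. The simulated gains are a little smaller because estimating the baseline slope costs something in so small a sample.

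**4. Adding patients seen at t2 but not at t3.** At r = 0.7 with 20% attrition, the variance of the A−C difference at t2 for change scores in completers, relative to baseline adjustment on all available t2 data, is:
- about 1.14 if all dropout comes before t2
- about 1.31 if half comes before and half after
- about 1.48 if all comes after t2

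The article does not give the timing of dropout, so only the range can be stated.

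**5. Age.** An age effect that is equal at all visits cancels from the group-by-time test. Only an effect on change matters. Simulated power at r = 0.7, 12 per group with complete data, A and B both 0.8 SD better than C at t2 and t3:

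| age effect on change | ANOVA interaction | baseline-adjusted, no age | baseline-adjusted, with age |
|---|---|---|---|
| 0 | 0.75 | 0.90 | 0.90 |
| 0.5 SD | 0.71 | 0.85 | 0.90 |
| 1.0 SD | 0.57 | 0.66 | 0.88 |

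The adjusted analyses use the mean of t2 and t3 and a 2-df group test, so part of the gap from the first column is the cost of the 4-df test. The last two columns isolate age. With a 1.0 SD age effect and no treatment effect, the ANOVA rejects in about 1.7% of trials against 5% for the model with age. Leaving age out therefore makes the test conservative.

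**6. How often the gate opens.** At 12 per group with complete data and r = 0.7:
- about 33% of trials if A and B both improve by 0.5 SD
- about 61% if they improve by 0.8 and 0.5 SD
- about 75% if both improve by 0.8 SD

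Over r = 0.5 to 0.8 the first figure runs from 19 to 48% and the second from 37 to 81%.

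**The case against.** The strongest reply is that a group-by-time mixed ANOVA is a standard and valid analysis, used here for exploratory outcomes. Feasibility is the primary outcome, the sample size was not based on effects, and the article calls all results preliminary. The Mini BESTest, which feeds the main-trial sample size, is not in the list of outcomes for this ANOVA. All of this stands, and it limits the weight of the point.

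Three stronger readings are tempting, and the article does not support them.

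- A reader might infer that the plan contradicts its own intention-to-treat statement. The article never says that only complete cases are used, and what follows the MCAR test may be set out in a fuller document. What can be said is that the named model loses patients with a missed visit unless something is added.
- A reader might apply 20% attrition to 36 and infer that only about 29 would be analysed (36 × 0.8 = 28.8). The Sample size section already provides for this by allowing recruitment of 45.
- A reader might infer that pairwise estimates are withheld unless the interaction is significant. The same section plans Cohen's *d* with 95% CIs, and means with 95% CIs, without any gate. Only the post hoc tests are gated, and the ungated estimates are unadjusted.

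The age argument is also conditional: the article asserts that age predicts change but gives no size.

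**Conclusion.** The point holds as one of efficiency. The specified ANOVA is valid with complete data, but it uses baseline as an outcome level, omits the stratification factor and gates the post hoc pairwise tests.

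For one visit, baseline adjustment alone saves about 10 to 25% of the variance for r from 0.8 to 0.5, or about 15% at r = 0.7; at 12 per group the gain is slightly less. Using every patient seen at t2 brings the total variance ratio to between about 1.14 and 1.48 at r = 0.7 and 20% attrition, depending on when patients leave. No single figure for patients saved is justified. Age adds to this only if it predicts change. All sizes rest on assumed correlations and effects.

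Neither 36 nor 45 changes, because neither was derived from power. This is a free improvement to exploratory secondary analyses, not the correction of an error.

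**What to change.** Replace the 2-way mixed ANOVA with a linear mixed model (SPSS MIXED) for t2 and t3. Include group, visit, group-by-visit, the baseline value of the outcome, and age, and use all available post-baseline data. Report the adjusted A−B, A−C and B−C differences with 95% CIs at both visits whatever the interaction p-value, alongside the Cohen's *d* already planned. Patients with no post-baseline value still contribute nothing to this model, so state their number by group. Also say in one sentence how missing values are handled and what, if anything, follows from Little's test.

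The cost is analysis wording only: SPSS is already named, and age, baseline and all visits are already collected.
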